### Training intervention

The exercise intervention will consist of a supervised HIIT (two walking- and one indoor cycling-based session weekly), starting with a habituation week at an intensity of 75% of the maximal heart rate (HRmax). In the following seven weeks, the participants will perform a HIIT based on the following protocol and for a total duration of 45 min per session (modified from Wisløff et al. (50)): warm-up for 10 min at 60%–70% HRmax followed by a high-intensity interval consisting of 4×4 min at 80%–95% HRmax with 3 min of active recovery at 60%–70% HRmax and a 10 min cool-down at 60%–70% HRmax. Heart rate will be monitored during training by Garmin HRM-Dual heart rate sensors combined with Garmin Forerunner 45S watches. Exercise scientists motivate the participants during the intervals and will control each participant's heart rate during and after every training session. This protocol was chosen because it fulfils the requirements of a high-volume HIIT (51), has been extensively studied in both healthy and clinical populations, and its effects on CRF improvement are well-documented (39, 52). In addition, it has been previously used by our research group, with high adherence and absence of drop-out observed in healthy participants and patients with cardiovascular risk factors (53, 54).

### Control condition

Asking physically inactive participants to maintain their inactive habits may not reflect realistic conditions and is no longer considered the best option in a randomised controlled exercise intervention (55). Indeed, most participants will be aware of the positive effects of PA - or will become aware of them during an exercise intervention study (55). Further, denying an exercise intervention to participants who would have benefited from it (for instance, participants at risk of cardiometabolic diseases) might be ethically questionable (55). In accordance with current practices (55), control group participants will be informed about the World Health Organization (WHO) PA guidelines at the beginning of the study (56). The control group participants will get a phone call after four weeks to enquire about their well-being.

[figure not shown]

**Figure 3: Study design.** Abbreviations: HIIT = high intensity interval training, Cer = Ceramide, VO2peak = peak oxygen uptake

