#### 5th visit – post-intervention assessment

After completing the 8-week intervention, the same measurements from the baseline assessment will be repeated (including vital sign evaluation, clinical examination, height and weight measurement, BMI calculation, resting and exercise ECG). A second CPET will be performed to verify that the exercise intervention effectively improved CRF. Habitual PA will be re-assessed using the Global Physical Activity Questionnaire (57, 58).

All blood samples will be stored at -80°C at the Department of Sport, Exercise and Health of the University of Basel before being delivered to the Metabolomics Unit of the Faculty of Biology and Medicine at the University of Lausanne. A high-coverage method using reversed-phase liquid chromatography coupled to tandem mass spectrometry (RPLC-MS/MS) will be applied to quantify the 61 circulating sphingolipids (48).

[figure not shown]

**Figure 4: Schedule and sequence of study procedures as planned for study visits.** Abbreviations: ECG = electrocardiogram, CPET = cardio-pulmonary exercise testing, HIIT = high intensity interval training

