### 5.2 (Serious) Adverse Events and notification of safety and protective measures

An Adverse Event (AE) is any untoward medical occurrence in a study participant which does not necessarily have a causal relationship with the trial procedure. An AE can therefore be any unfavourable or unintended finding, symptom, or disease temporally associated with a trial procedure, whether related to it or not.

A Serious Adverse Event (SAE) (ClinO, Art. 63) is any untoward medical occurrence that:

- Results in death or is life-threatening,
- Requires in-patient hospitalisation or prolongation of existing hospitalisation, or
- Results in persistent or significant disability or incapacity

The investigator and Sponsor-Investigator make a causality assessment of the event to the trial intervention (see table below based on the terms given in ICH E2A guidelines). Any event assessed as possibly, probably or related is classified as related to the trial intervention.

| Relationship | Description |
|--------------|-------------|
|--------------|-------------|

|                                                                                         |                                                                                                                           |
|-----------------------------------------------------------------------------------------|---------------------------------------------------------------------------------------------------------------------------|
| Definitely                                                                              | Temporal relationship
Improvement after dechallenge*
Recurrence after rechallenge
(or other proof of drug cause) |
| Probably                                                                                | Temporal relationship
Improvement after dechallenge
No other cause evident                                          |
| Possibly                                                                                | Temporal relationship
Other cause possible                                                                             |
| Unlikely                                                                                | Any assessable reaction that does not fulfil the above conditions                                                         |

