#### **Follow-up of (Serious) Adverse Events**

Participants suffering from adverse events are treated medically, and an appropriate follow-up is ensured when the participant fully recovers. The follow-up process is documented and submitted to the Ethics Committee.

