## **6.2 Risk-benefit assessment**

The SphingoFIT study is designed so the participants can participate in an 8-week training program for free. HIIT brings the risk of short-term exhaustion or muscle soreness. Another posed risk is suffering from a musculoskeletal injury through training. These risks are minimised by dividing the training into a walking- and cycling-based part, thus alternating load and minimising the load on the joints. The risk for cardiovascular events through exercise is reduced by performing a resting and an exercise ECG before starting the intervention to screen for pathological changes in the heart. The potential benefit of gaining fitness and thus improving different health parameters outweigh, however, these risks. All subjects also benefit from receiving medical status information and expensive and complex examinations that can give them detailed information about their fitness status. In addition, their participation helps generate knowledge, forming the basis for new prevention methods.

All involved parties will keep the participant's data strictly confidential. Data will be entered in protected files on the server of the Department of Sport, Exercise and Health of the University of Basel. Access to these files will be restricted to study group members who agreed on confidentiality.

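### After randomisation the HIIT arm has 25 to 26 scheduled staff contacts against 3 for controls, and section 5.2 sets no common adverse-event enquiry or collection window to offset this

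*Protocol*

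**What the plan says.** **HIIT arm.** Under Training intervention (section 2.4), the programme has "two walking- and one indoor cycling-based session weekly". It opens with a habituation week, and then "In the following seven weeks, the participants will perform a HIIT". At each session exercise scientists "will control each participant's heart rate during and after every training session".

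**Control arm.** Under Control condition (section 2.4), participants are informed about the WHO physical activity guidelines, and "The control group participants will get a phone call after four weeks to enquire about their well-being".

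**Both arms.** Section 3.3 has every participant collect meals at visit 4, which HIIT participants may combine with a session, and attend visit 5. Visit 5 repeats the clinical examination and ends the described schedule: "A second CPET will be performed to verify that the exercise intervention effectively improved CRF".

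**Safety.** Section 5.2 takes an AE to be "any unfavourable or unintended finding, symptom, or disease temporally associated with a trial procedure, whether related to it or not". It grades causality and severity, requires serious AEs to be reported within 24 hours, and provides treatment and follow-up for participants known to have an AE. It does not say at which contacts AEs are asked about, in what words, or when collection starts and ends. Section 6.2 names the expected training risks: short-term exhaustion, muscle soreness, and "Another posed risk is suffering from a musculoskeletal injury through training".

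**The concern.** The AE definition applies to both arms and does not depend on relatedness, but the occasions on which an event could come to light are set by arm. HIIT participants meet staff about three times a week. Controls have one call, whose stated purpose is general well-being, and then the closing visits. Controls are also informed about activity guidelines, so they too can have sore muscles or a minor injury.

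If AE counts are later shown by arm, an excess in the HIIT arm could come from training or simply from being seen more often. Staff supervising the intervention know the allocation after randomisation (section 2.4). Section 5.7 also lists early evidence of harm or benefit as a ground for stopping, a judgement that is easier to make on comparable data.

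A second, separate issue affects both arms alike. The last described procedure includes a maximal exercise test, for which the synopsis-level risk section places a physician and a defibrillator on site. No later contact is described. After the first maximal test, at visit 1, participants return for the baseline visit, so a delayed event has a natural occasion to surface. After the second test it has none.

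**Working it through.** The protocol gives no count of contacts per arm, so there is no stated figure to reproduce. The count below is built from sections 2.4 and 3.3.

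**1. Scheduled staff contacts per participant after randomisation**

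| Contact | HIIT | Control |
|---|---|---|
| Supervised sessions, 3 per week × 8 weeks | 24 | 0 |
| Week-4 call | 0 | 1 |
| Visit 4 | 0 (combined with a session) or 1 | 1 |
| Visit 5 | 1 | 1 |
| Total | 25 to 26 | 3 |

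This assumes that the habituation week also has three sessions. The ratio is 25/3 = 8.3 to 26/3 = 8.7, so between 8:1 and 9:1.

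**2. Contacts described after visit 5:** 0 in both arms.

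**3. What the imbalance could mean for noticing events**

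Assume that an event is mentioned only if a contact falls on the same day or within the next w − 1 days. Assume also sessions on days 1, 3 and 5 of each week, the control call on day 28, visit 4 on day 53 and visit 5 on day 57. The share of the 56 intervention days covered is:

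| Recall w (assumed) | HIIT | Control |
|---|---|---|
| 2 days | 48/56 = 86% | 5/56 = 9% |
| 7 days | 56/56 = 100% | 17/56 = 30% |
| 14 days | 56/56 = 100% | 31/56 = 55% |
| 28 days | 56/56 = 100% | 56/56 = 100% |

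For example, with w = 7 in the control arm, the call covers days 22 to 28 (7 days) and visits 4 and 5 together cover days 47 to 56 (10 days). That makes 17 of 56 days.

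**4. Effect on an observed comparison**

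If the true AE risk is equal in both arms, the observed risk ratio equals the ratio of the proportions captured. The documents give no capture rates. With 90% assumed in the HIIT arm:

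- control capture 70%: 0.90/0.70 = 1.29
- control capture 50%: 0.90/0.50 = 1.8
- control capture 30%: 0.90/0.30 = 3.0
- equal capture in both arms: 1.0

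These figures show direction and range only. They are not a forecast.

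**The case against.** The strongest reply is that a contact imbalance is inherent in comparing supervised training with activity advice, a control choice that section 2.4 justifies. On this view section 5.2 treats the arms identically. AEs are not an endpoint (section 2.2), section 4.1 plans no between-arm AE test, and the study is low-risk category A. Most of this stands, and it limits the point to how AEs are ascertained. It does not remove the point: section 4.1 commits to CONSORT reporting, and nothing in section 5.2 makes the enquiry comparable.

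A reader might infer several stronger things that the documents do not support:

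- **A ratio of 24 to 1.** Setting the sessions against the single call leaves out visits 4 and 5, which controls also attend. Visit 5 repeats the clinical examination in both arms.
- **That AEs will in fact be collected unequally.** No section says AEs are recorded at sessions or at the call. The text establishes unequal opportunity, and unequal collection is an inference from it. With 28-day recall the gap in coverage disappears.
- **That events after the final test will be missed.** The test itself is medically attended, reporting of serious AEs has no stated end date, and known AEs are followed up. Later events are not actively sought and rely on spontaneous report. Because this is the same in both arms, it lowers ascertainment without creating imbalance.
- **That follow-up excludes participants who have not recovered.** The phrase "an appropriate follow-up is ensured when the participant fully recovers" is awkward and worth clarifying, but that reading is strained and the point does not rest on it.

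Figures 1, 3 and 4 (timeline, design and visit schedule) are not shown in the text reviewed, so a contact that appears only there cannot be excluded.

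**Conclusion.** The point holds as a matter of AE ascertainment. Scheduled contact after randomisation differs between arms by a factor of 8 to 9, and section 5.2 contains no common enquiry or window to offset it. A by-arm difference in AE counts, above all for mild or transient events, could therefore reflect contact frequency. How much depends on recall, which the documents do not give: the difference is large at 7 days, smaller at 14 and absent at 28. Active enquiry after the visit 5 maximal test is also absent from the visible text, equally in both arms.

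The primary ceramide analysis is unaffected, and no planned hypothesis test is compromised. The change is worth making because it is cheap and would make any safety summary by arm interpretable. The conclusion rests on three sessions in the habituation week and on the unseen figures adding no further contacts.

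**What to change.** In section 5.2, with matching entries in sections 2.4 and 3.3:

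1. Put the same short scripted AE question to both arms at the same times: at week 4 (in the existing control call, and by call or at a session for HIIT), at visit 5, and in one short call to every participant a few days after visit 5.
2. State when AE collection starts, and let the call after visit 5 close it.
3. Base any AE summary by arm on these common contacts. List training events reported at sessions separately, as a description of the HIIT arm only.

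The cost is up to 98 short calls after visit 5 (2 × 49 if nobody drops out), the question at week 4 and visit 5, and a line on the case report form: a few hours of staff time, with no added visit or procedure. The follow-up wording in section 5.2 can be clarified in the same amendment, as a minor edit.

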### Measurements:

Physical examination and measurements of vital signs (blood pressure, heart rate, respiration rate, oxygen saturation and body temperature), a resting and exercise ECG will be part of the clinical assessment to screen for cardiac contraindications to maximal exertion. Habitual PA will be assessed using the Global Physical Activity Questionnaire (57), which has been validated in a Swiss context (58). Maximal cardiopulmonary exercise testing (CPET) will be conducted on a cycle ergometer to determine  $\text{VO}_2$  peak, peak heart rate and power output (Ergoselect 200; Ergoline, Bitz, Germany). After the training programme, a second CPET will be performed to verify that the exercise intervention effectively improved CRF.

Height and body weight will be measured to the nearest 0.5 cm and 0.1 kg, respectively, and the body mass index will be calculated. Body composition will be analysed before and after the intervention by the gold-standard, dual-energy x-ray absorptiometry (DXA) using a GE Lunar iDXA® machine (GE Lunar Inc., Madison, WI; software version 13.10). Study participants will fast within 6 h prior to the measurement. Absolute and relative measures of total body fat mass and fat-free mass will be obtained. During the measurement, patients will be in a supine position (59). The effective radiation dose from a single whole-body DXA ( $< 10 \mu\text{Sv}$ ) is similar to the normal background radiation received over one day at sea level (60). Consequently, the effective radiation dose per study participant in the present study will be  $< 20 \mu\text{Sv}$ , which is similar to the normal background radiation received over two days at sea level. For comparison purposes, body composition will also be analysed before and after the intervention by four-segment bioelectrical impedance analysis using the InBody 720 (Inbody Co. Ltd., Seoul, South Korea). Before the measure, participants must refrain from intense PA for 24 h, fast for at least two hours, and be asked to void their bladder.

Trained medical staff will draw blood samples by venepuncture of the cubital fossa following an overnight fast pre-and post-intervention. The total volume of blood samples will be ca. 40 mL ( $2 \times 2.7 \text{ mL}$  potassium-EDTA,  $2 \times 7.5 \text{ mL}$  serum-monovette, and  $1 \times 7.5 \text{ mL}$  Li-Heparin). Blood samples will be immediately centrifuged, and the serum aliquots will be frozen at  $-80^\circ\text{C}$ . Planned blood analyses for essential characterisation of risk factor profiles include total cholesterol, LDL- and HDL-cholesterol, triglycerides, and HbA1c. Glucose and insulin will also be measured to estimate insulin resistance using the Homeostatic Model Assessment for Insulin Resistance (HOMA-IR) (61). A high-coverage method using reversed-phase liquid chromatography coupled to tandem mass spectrometry (RPLC-MS/MS) will be applied to quantify an extensive panel of circulating sphingolipids ( $n=61$ ) (48).

To our knowledge, no evidence exists that food intake influences sphingolipid levels. Nevertheless, each participant will receive standardised, pre-packaged meals for the two days preceding blood sampling to minimise potential confounding. All participants will be fed to energy balance. Energy requirements will be calculated with the formulas of Mifflin St. Joer (62) and the National Institute of Diabetes and Digestive and Kidney Diseases Body Weight Planner (63, 64). All diets will contain  $\sim 55\%$  energy from carbohydrates,  $\sim 25\%$  from fat, and  $\sim 20\%$  from protein. To monitor diet adherence, participants will be instructed to return all non-consumed foods from the pre-packaged meals to the lab and take photos of additionally consumed foods for later analysis. Participants will also be asked to refrain from alcohol consumption during the dietary control period (i.e., the two days preceding blood sampling). For the rest of the study, participants will be advised to eat as usual.

Retinal vessel diameters, a novel surrogate of microvascular health that responds positively to exercise intervention, will be assessed pre-and post-intervention as described in detail by Hanssen et al. (65). Arteriolar and venular diameters will be measured using semiautomatic software based

on a modified fundus camera (450FF; Carl Zeiss, Jena, Germany). Three valid images of the right eye retina will be taken at an angle of 45° and with the optic disc in the centre. Retinal arterioles and venules within a distance of 0.5 to 1 disc diameter from the optic disc will be identified semi-automatically (Vesselmap 2; IMEDOS Systems, Jena, Germany). Vessel diameters will be averaged to central retinal arteriolar (CRAE) and venular equivalents (CRVE), as well as their ratio, using the Parr–Hubbard formula described elsewhere (66). This reliable method has inter- and intra-observer interclass correlation coefficients between 0.78 to 0.99 (66, 67).

Brachial artery flow-mediated dilatation (FMD) reflects endothelial function as an early marker of atherosclerotic arterial damage (68). It provides an *in vivo*, noninvasive, direct measure of artery function and health (69). There is increasing evidence that FMD in humans is associated with traditional risk factors, cardiovascular diseases, and heart failure and predicts cardiovascular events and all-cause mortality (68, 70). It is sensitive to changes in behavioural health shown for the Mediterranean diet, acute mental stress or exercise training (71, 72, 73). Measurement of FMD of the brachial artery follows after at least 15-20min of rest in the supine position using a high-resolution linear ultrasound array transducer with a semi-automatic detection program of the intima-media complex (EF, Unex Corporation, Nagoya, Japan). An occlusion cuff will be wrapped around the forearm with the proximal edge of the cuff at the elbow. Longitudinal images of the right brachial artery (typically at 3-5 cm above the elbow) are recorded at baseline and after cuff deflation following supra systolic compression (50 mmHg over the systolic blood pressure value) of the right forearm for 5 minutes until 3 minutes after deflation. Inter-reader and inter-session reliability of the FMD measurement were acceptable (74, 75).

Echocardiographic assessment, particularly atrial strain analysis—an emerging ultrasound-based technique—facilitates the comprehensive evaluation of atrial mechanics, offering invaluable insights into atrial fibrosis (76). Atrial fibrosis, in turn, is a hallmark of atrial structural remodelling, which leads to atrial fibrillation, the most common cardiac arrhythmia with an ever-increasing prevalence (77, 78). Strain analysis, a highly sensitive measure of cardiac function, has demonstrated responsiveness to even short periods of endurance exercise training, as observed in a 4-week HIIT intervention (79).

Standardised echocardiographic images will be systematically acquired in the supine position, adhering to international standards (80, 81). The imaging process will use a state-of-the-art ultrasound system (Philips Epiq 7 Ultrasound System, Koninklijke Philips N.V., Amsterdam) equipped with a compatible broadband sector array transducer (S5-1, Philips, Koninklijke Philips N.V., Amsterdam). Post-acquisition, echocardiographic images will undergo meticulous analysis for strain parameters within the ultrasound workspace, utilising advanced software (TOMTEC Imaging Systems GmbH, Unterschleissheim, Germany).

### **3. STUDY POPULATION AND STUDY PROCEDURES**

#### **3.1 Inclusion and exclusion criteria, justification of study population**

This randomised controlled trial will include 98 participants (50% of females) aged between 40 and 60 years at elevated cardiometabolic risk. They will be randomised to the intervention and control groups. To investigate whether circulating sphingolipid levels can be reduced following an 8-week HIIT intervention, it is ideal to include patients at elevated cardiometabolic risk but without any symptomatic cardiometabolic diseases. Indeed, these patients are likely situated in the first phase of sphingolipid accumulation, which is believed to be reversible.

